#### Economic evaluation

The economic evaluation will be performed alongside the randomized trial from a societal perspective. Data on resource use are collected in several ways: self report questionnaires, hospital and nursing home registration, and community pharmacy records. Only direct healthcare costs will be considered such as costs of consultations of the general practitioner, nursing home physician, medical specialist, hospitalizations, and medical department of the nursing home, and use of medication and medical aids. Medication data are retrieved from the centralized pharmacy files in the research region. If available, Dutch guideline prices are used to value resource use [31,32]. Otherwise, tariffs are used. Medication costs are valued using prices of the Royal Dutch Society for Pharmacy [33]. Contacts with GPs and referrals will be checked as well in GPs' patient information files.

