### Frailty and preventive mechanisms

Frailty is the result of reduced ability to maintain a physiological and psychosocial equilibrium, thereby increasing the risk of functional disability, temporary or permanent loss of the ability to cope, morbidity, and mortality [14-16]. Frailty is strongly associated with aging [17,18]. The potential preventive mechanisms of home visits comprise early detection of worsening health conditions and modifiable risk factors, enabling concerted actions with responsible health professionals to optimize treatment, improve life style and increase support for family caregivers to persevere informal care.

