### Costs

Aging is costly. About one third of the health care expenditures in industrialized countries relate to persons 70 years or older [19]. Nursing homes, homes for the elderly and hospital beds are occupied mainly by elderly. Elderly are massive consumers of medication. Elderly consume most home care. When the number and portion of (frail) elderly increases the health care costs will explode. Among community dwelling elderly with usual care the median annual nursing home and hospital admission rate is 2.4% (range 0–40%) respectively 26% (range 5–56%). Among frail elderly median annual admission rates are 15% and 45% respectively [11,12].

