#### Outcomes and measurements

Table 4 provides an overview of all outcomes and measurements in the study.

**Table 4 T4:** Measurement scheme

*Health screener*	*Instrument*	*T-1*	*T0*	*T1*	*T2*
				*6 months*	*18 months*
Functional Health status	COOP-WONCA	X		X	X
ADL & IADL	GARS	X		X	X
Cognitive decline	IQCODE self report	X			
Depressive symptoms	CES-D	X		X	X
Chronic diseases	Chronic diseases list	X			X
Mobility and Falls	Questionnaire	X		X	X
Body Mass Index	Questionnaire	X			
Weight change	Questionnaire	X			
Demographics	Questionnaire	X			
Behavioral problems	Questionnaire	X			
Incontinence	Questionnaire	X		X	X

*Main Outcomes*					
a. Health related Quality of life	SF36 + EQ5D		X	X	X
b. Hospital admissions	Patient + hospital database		X	X	X
c. (Days until) Institutionalization	PCP + nursing homes				X
d. (Days until) Mortality	Relatives + PCP				X
e. Health resource utilization	Self report + PCP + hospital + pharmacy databases		X	X	X

PCP = Primary Care Physician

GARS = Groningen Activity Restriction Scale

CES-D = Center for Epidemiological Studies – Depression Scale

IQCODE = Informant Questionnaire on Cognitive Decline in the Elderly

SF36 = Short Form 36 item version

EQ5D = EuroQuality of life

X = measurement

T-1 = pre randomization health screening

T0 = Measurement immediately after randomization

T1, T2 = Follow-up measurements

Outcomes are:

1. Health related quality of life as measured with the Short Form 36 (SF-36), and Quality Adjusted Life Years by health utilities based on Euroqol (EQ-5D) [26,27];

3. (Days until) institutionalization: Hospital stay, placement in nursing home or home for the elderly are surveyed and crosschecked at institutes;

4. (Days until) mortality as checked with the PCPs;

5. Direct costs as measured by patient questionnaires with three-monthly recall periods. These self-report data are supplemented by data from the centralized regional pharmacy database (medication use), regional hospital check, and nursing home checks. In case patients are not able to fill out the forms themselves a close relative will be approached (Table 4).

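### The economic evaluation is called societal but admits only direct healthcare costs, so its result would be a healthcare-perspective result under the wrong label

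*Protocol article*

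**What the plan says.** The Economic evaluation section of the protocol article opens with the perspective: "The economic evaluation will be performed alongside the randomized trial from a societal perspective". After one sentence on data sources it sets the cost scope: "Only direct healthcare costs will be considered such as costs of consultations of the general practitioner, nursing home physician, medical specialist, hospitalizations", and the list ends "and medical department of the nursing home, and use of medication and medical aids". The data sources named are "self report questionnaires, hospital and nursing home registration, and community pharmacy records", with GP files as a further check.

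The outcome list under Outcomes and measurements describes the cost outcome as "Direct costs as measured by patient questionnaires with three-monthly recall periods", supplemented by pharmacy, hospital and nursing home data. The Cost analysis section then compares the arms on the difference in total costs and derives cost-effectiveness and cost-utility ratios from it.

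Two background statements bear on the scope. Among the potential mechanisms of home visits, Frailty and preventive mechanisms includes the aim to "increase support for family caregivers to persevere informal care". The Costs section notes "Elderly consume most home care".

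**The concern.** A societal perspective counts resource use whoever bears it: the health system, the patient, or the family. A healthcare perspective counts only what falls on health services. The perspective therefore decides which costs enter the numerator of every ratio the trial will report.

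This matters more here than in most trials, for two reasons. First, the Abstract and the Objectives both give cost-effectiveness as the purpose of the evaluation. Second, the intervention is expected to act partly through family carers. Their time is a resource that a societal analysis should value and that the stated restriction leaves out. A reader who sees a societal label would assume that any change in carers' burden, up or down, is already in the total. It would not be.

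**Working it through.** There is no stated figure to reproduce: the article gives no unit prices, expected costs or expected cost difference. The check is to set the statements side by side.

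**1. Label against scope.** The first sentence of Economic evaluation says societal. The third restricts costs to direct healthcare costs, using the word *only*. The restriction is categorical, and the examples that follow are all health-service items. No reading of the second statement satisfies the first.

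**2. Does another section widen the scope?** The outcome list says direct costs. Taken alone, that term could cover direct costs outside healthcare, such as paid help or family time. The Economic evaluation section then narrows it to healthcare. Cost analysis refers to total costs without redefining them. Nothing restores the non-healthcare component.

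**3. What is certainly excluded.** Informal care and other patient and family costs are not direct healthcare costs, so *only* removes them.

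**4. What is merely not named.** The listed items are GP, nursing home physician, specialist, hospitalization, medical department of the nursing home, medication and medical aids. The list does not name the intervention nurses' time, home care, or days in a home for the elderly. It is, however, introduced as a set of examples, and these three could be counted as direct healthcare costs. Placement in a home for the elderly is also collected and cross-checked as an outcome. Their omission from the analysis is not shown.

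**5. Effect on the result.** Write the incremental cost as

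ΔC(societal) = ΔC(healthcare) + ΔC(patient and family).

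The plan estimates ΔC(healthcare) and calls it ΔC(societal). The error in the labelled quantity is ΔC(patient and family). It is positive if the intervention leads families to provide more care, negative if support lightens their load, and zero if neither happens. The article gives no hours and no prices, so neither sign nor size can be computed.

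**6. Scale of the nurse contacts, for the confirmation requested below.** Recruitment reports 658 randomized, with equal blocks: 658 / 2 = 329 per arm. The nurses offer at least 5 visits in a year: 329 × 5 = 1,645 visits, all in one arm. These are visits offered, so 1,645 assumes full uptake and is not a floor on visits made. If this nurse time were left out, incremental cost per patient would be understated by the number of visits made times the cost of a visit. The article gives neither number.

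**The case against.** The strongest defence is that this is a journal article condensing a fuller protocol, and that a list of examples should not be read as a complete costing manual. For the unnamed items, that defence stands. A reader might infer that the nurse visits, home care and homes for the elderly will be left out and that the result will therefore be biased. The article does not support this: the list is open, the items can fall within its scope, and the analysis refers to total costs.

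A reader might also infer that the omissions all favour the intervention. That does not follow either. Omitting nurse time would flatter the intervention. But if the visits delay institutional care, omitting days in homes for the elderly would hide savings and count against it. Omitting home care could go either way. For informal care, the background speaks of supporting carers as a potential mechanism; it does not say that paid care is moved onto families, and support may reduce their burden. Euro estimates of these effects would rest entirely on assumed hours and prices.

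It can further be said that the authors use *societal* loosely. Earlier interventions pairs that word with cost savings, as against health gains for the patient. That may explain the wording, but it is a reason to correct the label and does not make it accurate.

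The contradiction itself survives. It is not a detail left to a longer document, because the article makes both statements and no fuller text can make both true. It does not touch randomization, sample size or the analysis of clinical effects.

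**Conclusion.** The point holds as a contradiction between the declared perspective and the stated cost scope. If the restriction is followed, the cost-effectiveness and cost-utility results are healthcare-perspective results and cannot be presented as societal. This rests on two things only: the ordinary meaning of a societal perspective, and reading the word *only* as written.

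The size and direction of any bias are undetermined. The article does not establish that intervention nurse time, home care or homes for the elderly are excluded; it leaves that unclear, and the sponsor should settle it when reconciling the text.

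**What to change.** Make the label and the scope agree before the cost analysis is run, by one of two routes.

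- **Relabel.** Describe the evaluation, its ratios and its conclusions as a healthcare perspective throughout. This costs only wording. The result can then no longer speak to costs borne by families.
- **Keep the societal label.** Add informal-care and patient and family cost items to the resource-use questionnaires, and state how they will be valued. This costs a few items and possibly a less favourable result. Timing limits it: inclusion ran from spring 2003 to summer 2004, so the earliest participants reached the 6-month measurement before inclusion closed. Any item added late would cover only the remaining follow-up, and the report should say so.

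Under either route, add one sentence saying whether total costs include intervention nurse time (assessment, visits, training and supervision), home care, and days in homes for the elderly. Name the source for each, since the article does not identify one specifically for the nurses' training and supervision. If these are already in the full protocol, this costs nothing beyond the sentence.

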##### Cost analysis

To compare costs between the two groups, confidence intervals for the differences in mean costs are calculated using bias-corrected and accelerated bootstrapping with 5000 replications. [34] For the cost-effectiveness analysis the difference in total costs between the intervention and usual care group are compared with the difference over 18 months in improvement of quality of life, reduced institutionalization, hospitalization and mortality. In addition, a cost-utility analysis will be done to assess the incremental costs per Quality Adjusted Life Years (QALY). Uncertainty around the cost-effectiveness and cost-utility ratios is calculated using the bias-corrected percentile method (5000 replications) and presented in a cost-effectiveness plane [35].

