#### Data-analysis

According to the 'intention-to-treat' principle differences between intervention and usual care patients on mortality, hospitalization and nursing home placement (dichotomous outcomes) are tested by both chi-square tests and logistic regression analysis. Differences in time until these events will be analyzed with Cox-proportional hazard modeling. For quality of life (continuous outcome: SF-36, EQ-5D) General Linear Models (GLM), a technique for repeated measures is used to analyze group differences. Possible baseline differences in the outcome measures will be accounted for in GLM. Additional subgroup-analyses will be performed on types of recommendations in the care-plans.

Potential confounding and effect-modification is checked for sociodemographic characteristics, number and type of chronic disease, (I)ADL functioning (GARS), cognitive decline (IQCODE), mood (CES-D), behavioral problems (incontinence, sleep, agitation en aggression), medication use (centralized pharmacy data base) (Table 4) [28-30].

Quality of the data was assured by independent double checks of all forms. Also our institute employs a quality assurance policy. In this respect guidelines on all aspects of research were issued and all projects are subject to audits.

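### The cost comparison is described without a baseline term although resource use is collected at T0; the planned contrast is valid but gives up precision

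*Protocol article*

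**What the plan says.** In the protocol article, Outcomes and measurements, Table 4 has the row "e. Health resource utilization" among the main outcomes, with marks at T0, 6 months and 18 months. Its sources are self-report, the physician, and hospital and pharmacy databases. The outcome list in the same section describes "Direct costs as measured by patient questionnaires with three-monthly recall periods", supplemented by pharmacy, hospital and nursing home data. The table notes define "T0 = Measurement immediately after randomization".

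The Cost analysis section says that "confidence intervals for the differences in mean costs are calculated using bias-corrected and accelerated bootstrapping with 5000 replications". For cost-effectiveness, "the difference in total costs between the intervention and usual care group are compared with the difference over 18 months" in quality of life, institutionalization, hospitalization and mortality. Cost-utility is expressed as incremental cost per QALY. No covariate is named for any of these.

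On baseline values, the Data-analysis section states: "Possible baseline differences in the outcome measures will be accounted for in GLM". The model meant is the one for SF-36 and EQ-5D. The next paragraph lists characteristics to be checked for confounding and effect modification. Medication use is among them; prior cost is not, and costs are not mentioned as an outcome.

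**The concern.** Cost-effectiveness is the stated purpose of the trial. The T0 measurement of resource use has no described role in the analysis of costs. Past care use often predicts later care use, and in that case a plain difference in means leaves explainable variance in the estimate. Randomization was blocked by practice, and nothing in the Design section balances the arms on prior care use. A chance imbalance at baseline would therefore pass, in proportion to the correlation, into the incremental cost and into both ratios. At stake are the width of the cost interval and the reading of a single realised cost difference.

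**Working it through.** **What the article fixes.** Set side by side:
- Table 4: resource use is measured at T0.
- Cost analysis: difference in mean or total costs, bootstrapped, with no baseline term.
- Data-analysis: baseline accounted for in the SF-36/EQ-5D model.
- Patient outcome analysis: QALYs are utility multiplied by time with linear interpolation, with no baseline term.

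The article states no sample size, power, standard deviation or correlation for costs, so there is no cost figure of its own to reproduce.

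**Inputs.** 658 patients were randomized (Recruitment), in equal numbers per practice (Design), so about 329 per arm. The correlation ρ between pre-randomization and follow-up cost is assumed, from 0.1 to 0.7. Results are in standard deviation (SD) units of cost. Patients are treated as independent, which ignores the joint randomization of people at one address, and attrition is ignored. The percentage narrowing below does not depend on the number of patients.

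**Chance imbalance at baseline.** Standard error (SE) = √(2/329) = 0.078 SD; 95% range ±1.96 × 0.078 = ±0.153 SD. An imbalance at the edge of that range moves the unadjusted follow-up difference by ρ × 0.153 SD.

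**Precision.** Adjusted variance = (1 − ρ²) × unadjusted variance, so the interval width is multiplied by √(1 − ρ²). The unadjusted half-width is 0.153 SD. The unadjusted sample size that would match 658 adjusted patients is 658/(1 − ρ²).

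| Assumed ρ | Shift at 1.96 SE imbalance (SD) | √(1 − ρ²) | Adjusted half-width (SD) | Matching N |
|---|---|---|---|---|
| 0.1 | 0.015 | 0.995 | 0.152 | 665 |
| 0.3 | 0.046 | 0.954 | 0.146 | 723 |
| 0.5 | 0.076 | 0.866 | 0.132 | 877 |
| 0.7 | 0.107 | 0.714 | 0.109 | 1290 |

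**In terms of power.** Take a cost difference that the unadjusted analysis would detect with 80% power (an illustration; the article states no power for costs). Adjusted power = Φ((1.960 + 0.842)/√(1 − ρ²) − 1.960):
- ρ = 0.1: 2.802/0.995 − 1.960 = 0.856, power 80%
- ρ = 0.3: 2.802/0.954 − 1.960 = 0.977, power 84%
- ρ = 0.5: 2.802/0.866 − 1.960 = 1.275, power 90%

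**Skewed costs.** A simulation used lognormal costs with log-scale SD 1, 329 per arm, no true difference and 4000 trials. At log-scale correlations of 0.3 and 0.5:
- The mean unadjusted difference was 0.003 and 0.0005, that is, no bias.
- A normal-approximation 95% interval for it covered in 94.7% and 95.1% of trials.
- Adjustment cut the SE by 2.5% and 6.6%.

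These cuts look small because a log-scale correlation r corresponds to a raw-scale correlation of (eʳ − 1)/(e − 1), here 0.20 and 0.38. For those values, 1 − √(1 − ρ²) gives 2.1% and 7.4%, in line with the simulation. The formula therefore holds reasonably well for skewed costs, provided that ρ is read on the raw cost scale.

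**The case against.** The strongest reply is that the point argues from silence. The Cost analysis section names a quantity (the difference in mean costs) and an interval method. Neither excludes a covariate, and the remedy below keeps both. The article is condensed, and a full analysis plan may name the adjustment. It stands that the article does not rule adjustment out. But it does not leave the cost method to another document either: it gives the estimator, both bootstrap variants, the number of replications and the cost-effectiveness plane, and it mentions baseline accounting where that is intended. The plain reading of the cost text is an unadjusted contrast.

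Several stronger readings are tempting, and the article does not support them:
- *The cost result is biased or its interval invalid.* It is neither. Chance imbalance is already reflected in the width of the interval.
- *The effect side is protected while the cost side is not.* This holds only for SF-36 and EQ-5D in the general linear model. The QALY calculation names no baseline adjustment, and the event outcomes are not in that model.
- *The T0 covariate is free of any influence of allocation.* The three-month recall window lies almost wholly before randomization, but the form is completed afterwards, and only the physicians are described as blind. The assurance holds for register data cut at the randomization date, not for self-report.
- *Costs are stated as 18-month totals.* In the text the 18 months attach to the effects; applying them to costs is a reasonable inference.

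It also stands that the gain rests on an assumed correlation and is negligible if that is low. Nothing in the article shows how well a short baseline window predicts long-run cost.

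**Conclusion.** The point holds as one of efficiency. As described, the cost comparison and the cost side of both ratios have no baseline term, although the data for one are collected. The contrast remains unbiased and its interval valid. The loss is an interval wider than it need be by an amount that the article cannot settle: adjustment would narrow it by about 0.5% if ρ is 0.1, 5% if 0.3 and 13% if 0.5. With about 329 per arm, an imbalance in prior cost at the edge of its 95% chance range would move the incremental cost by 0.015, 0.046 or 0.076 SD at those values, against an unadjusted half-width of 0.153 SD. All of this assumes independent patients and a correlation on the raw cost scale. The change is worth making because cost-effectiveness is the trial's objective and the adjustment is cheap. Leaving it out would not invalidate the cost result.

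**What to change.** In Cost analysis, state that the cost difference is the arm coefficient from a linear regression of follow-up total cost on arm and pre-randomization cost, refitted in each of the 5000 bootstrap replications. This keeps the arithmetic-mean interpretation and the bias-corrected and accelerated interval.

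Build the covariate preferably from pharmacy and hospital records cut at the randomization date. If T0 self-report is added, say that it was completed after allocation, and impute missing covariate values so that no patient is dropped.

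Use the adjusted cost difference in both the cost-effectiveness and the cost-utility analysis. Adjust QALYs for T0 EQ-5D in the same way, so that an adjusted cost is not set against an unadjusted QALY difference. Report the unadjusted cost difference as a sensitivity analysis.

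The cost is some analysis wording and one extra regression per replication. Table 4 already marks T0 for these sources, so no new collection should be needed, assuming that the record extracts reach back before randomization. The small downside is the handling of missing T0 self-report.

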##### Patient outcome analysis

QALYs are calculated by multiplying the utility based on EQ-5D scores with the amount of time a patient spent in this particular health state [36]. Transitions between health states are linearly interpolated.

#### Recruitment

The recruitment phase yielded a total of 33 PCP practices that were willing to participate. Inclusion started in spring 2003 and lasted until summer 2004. Figure 1 provides an overview of the recruitment and randomization. The health questionnaire was mailed to 4823 patients. Of the 2949 (61%) responders, 658 frail patients were detected and randomized.

